## Abstract

**Abstract:**

**Introduction:**

Tobacco smoking remains a leading cause of ill-health, premature mortality and a driver of health inequalities. To support smokers in England, a comprehensive approach to treating tobacco dependence is being implemented. This includes offering support to all people admitted to hospitals, as well as women and pregnant people within NHS settings. We aim to describe the protocol for an evaluation of this tobacco-dependence service.

**Methods and analysis:**

This is a national evaluation across five regions in England (i.e., South West, West Midlands, Greater Manchester, North East and North Cumbria, Yorkshire and Humber) including 11 NHS Foundation Trusts. It is funded from September 2021 to September 2025. Evaluation settings are acute hospital, maternity and inpatient mental health.

Work package (WP) 1 involves qualitative key informant interviews to characterise the policy implementation context. WP 2 involves an online survey to assess the routinisation of the service in practice and staff attitudes regarding tobacco dependence, plus in-depth interviews with relevant practitioners to explore survey findings and interviews with smokers to investigate its usefulness and impact. WP 3 involves descriptive statistical analysis of routinely collected data to assess service uptake and impact on health and care outcomes (e.g., smoking status). WP 4 involves an economic analysis of routinely collected data to determine the financial impact of the service. Qualitative data (WP 1, WP 2) will be analysed using Thematic Analysis and Framework Analysis, respectively. WP 2 survey data will be analysed using descriptive statistics.

**Ethics and dissemination:**

This evaluation received favourable ethical opinion from Newcastle University (17756/2021) and NHS Wales Research Ethics Committee (22/WA/0203). It has also received Confidentiality Advisory Group support (22CAG0103).

STRENGTHS AND LIMITATIONS OF THIS STUDYThe evaluation uses robust mixed methods informed by theory, specifically Normalisation Process Theory and the Theoretical Framework of Acceptability.The evaluation is also strengthened by integrating Public Involvement and Community Engagement across all stages of the evaluation, to ensure that it is designed and delivered using approaches that are acceptable to patients and the public.Participants in the qualitative elements of the evaluation are self-selecting; however, a purposive sampling technique will allow for views from a diverse group of people to be captured.Quantitative data collection is restricted to NHS acute hospital, maternity and mental health inpatient settings (i.e., excludes data collected and reported within community-based tobacco dependence services) and could potentially limit our analyses of outcomes.A triangulation protocol will allow for the synthesis of data from different sources and inform recommendations for sustainable evaluation and tailoring of the service to different contexts.

## Introduction

 Tobacco smoking remains a leading cause of ill-health, premature mortality and a driver of health inequalities. An analysis of the Global Burden of Disease Study in 2019 showed that although smoking prevalence has reduced, this has not kept pace with population growth, and so the total number of smokers has increased.^1^ Moreover, progress made from tobacco control measures has slowed in the last 5 years, concluding that stronger, more consistent measures need to be implemented to achieve the Sustainable Development Goals.^1 2^ Smoking prevalence remains higher in those from lower socioeconomic backgrounds, who are also disproportionally impacted by health inequalities.^3^

The NHS Long Term Plan, published in 2017,^4^ set out health and care priorities in England over the next 10 years. This policy has a focus on prevention and health inequalities, specifically a commitment to NHS action to prevent ill-health. One key area of action was smoking, where a comprehensive package of care and treatment was implemented to provide proactive smoking cessation support to all those who were admitted to the hospital, expectant mothers and their partners and long-term users of specialist mental health services. Prior to this, the default model for tobacco dependence treatment was an opt-in approach where smokers could seek help to quit from healthcare professionals, with the exception of maternity services where opt-out pathways have been recommended since 2010.^5^ This paper describes the protocol for a mixed-method evaluation of this tobacco-dependence treatment service in acute hospitals, maternity and inpatient mental health settings in five regions in England, which aims to assess its implementation and impact on health and care outcomes.

### NHS-funded tobacco dependence services

The NHS-funded tobacco dependence services (NHS TDS) is the package of care and treatment for people who smoke in England. This includes three bespoke models for inpatient hospital, maternity and inpatient mental health settings, which include a combination of screening, treatment (e.g., freely available nicotine replacement therapy (NRT)) and behavioural support, as summarised in table 1. The aim of this study is to undertake an evaluation of the implementation of the NHS TDS.

**Table 1 T1:** NHS-funded tobacco dependence services (NHS TDS) care models by setting

Setting	Care model
Inpatient acute	A patient’s smoking status is recorded at admission. Patients are provided very brief advice and a referral for a consultation with an in-house service. They are then provided a personalised treatment plan which includes: behavioural support, nicotine replacement therapy (NRT) or other forms of pharmacotherapy during their hospital stay, with follow-up at 28 days post-discharge. Patients are then discharged into community services where appropriate.
Maternity	Adapts the inpatient acute model (above), delivered in-house within maternity services. In addition, all women will be offered a carbon monoxide (CO) test at the first antenatal booking appointment, with maternity staff recording the outcome, followed by a one-on-one meeting with a tobacco dependency advisor (TDA) arranged at the first antenatal booking appointment.Weekly face-to-face appointments with the TDA take place for at least 4 weeks, with NRT supplied for up to 12 weeks beyond the quit date. Support is continued throughout the pregnancy with appointments at least monthly. A 28-day quit status is recorded by the TDA, followed by a CO-validated smoking status at 36 weeks and an updated smoking status is recorded at time of delivery.
Inpatient mental health	Adapts the inpatient acute model (above), delivered in inpatient mental health settings. While all TDA should aim to see all patients within 48 hours of admission, it is understood that this may not be possible due to the nature of mental illnesses; likewise, the initial TDA assessment may not be complete in one session and may require multiple visits.Additional weekly face-to-face appointments with TDA are expected, to ensure engagement and monitor progress for the first 4 weeks of admission. Prior to discharge a face-to-face planning session between the patient and TDA to identify where support and medication can be accessed post-discharge; this support continues beyond discharge in line with mental illness and/or local pathways.

These models are adapted from evidence-based smoking cessation interventions; in particular, the Ottawa Model for Smoking Cessation (OMSC, Canada) and the Conversation, Understand, Replace, Experts and Evidence-Based treatment (CURE) project within the UK. The OMSC uses a ‘5 As’ approach—ask, advise, assess, assist and arrange.^6^ This model aims to support smokers in achieving long-term smoking abstinence after being admitted to the hospital through documenting inpatients’ smoking status; providing brief advice and pharmacotherapy; opt-out referral to specialist teams for inpatient and post-discharge behavioural support via community-based services.^7^ The CURE project is the closest adaptation to the OMSC model in England, implemented in acute hospital settings. CURE adopted a whole-system approach in line with the National Institute for Health and Care Excellence (NICE) PH48 guidelines (section 4.1). On admission to the hospital, patients are screened for smoking status. On identification and recording as an ‘active smoker’, the individual is referred to the CURE team, provided brief advice and offered NRT and varenicline at no cost to the smoker. Within 48 hours of admission, further support is provided including a 45-min consultation with a specialist stop smoking practitioner, a review of NRT and additional medications, behavioural support, signposting to post-discharge support and a follow-up plan developed. After discharge, a telephone follow-up is conducted between weeks 1 and 2; then a face-to-face 4-week follow-up with CO verification of smoking status; and finally, a 10–12-week telephone follow-up. The model is tailored for maternity settings, such that continued support is provided throughout pregnancy with smoking status recorded at delivery; and for mental health, the frequency of assessments and follow-up support can increase due to the nature of mental illnesses.

### Evaluation aims and objectives

The specific objectives for each study component are summarised in table 2. Implementation of the service (i.e., when the service was set up) nationally was set up to begin between in 2021/2022. Trusts participating in this evaluation started service implementation between February 2022 and November 2022, following challenges to service and data collection setup across the country. These studies are complementary to the national evaluation undertaken by NHS England (https://digital.nhs.uk/data-and-information/publications/statistical/statistics-on-nhs-stop-smoking-services-in-england).

**Table 2 T2:** Evaluation objectives and study components

Evaluation objective	Study components
To describe the implementation context, including practices, services and structures of pre-policy implementation	Work package (WP) 1: Key informant interviews and document analysis
To explore system-wide implementers’ (ie, front-line staff, managers or service leads, service commissioners) perceptions and experiences of service implementation	WP 2a: Survey of healthcare professionalsWP 2b: Interviews with healthcare professionals
To explore smokers’ perceptions of service implementation	WP 2c: Interviews with smokers offered the NHS-funded tobacco dependence services (NHS TDS)
To determine the level of participation in the NHS TDS	WP 3: Analysis of routinely collected patient data (effectiveness and process analysis)
To estimate service effectiveness as the change in number of smokers who have undertaken an intervention and self-reported and/or have a carbon monoxide (CO) confirmed 28-day quit	WP 3: Analysis of routinely collected patient data (effectiveness and process analysis)
To estimate the cost-effectiveness of the service per additional quit	WP 4: Health economic analysis

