### WP 3: effectiveness and process analysis (months 25–48)

#### Design

This quantitative non-randomised observational study aims to assess the reach of the service as well as the effect on health outcomes (effectiveness) and healthcare use (service uptake).

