#### Population

All adults (aged 18 and over) who are identified as smokers in acute hospital, maternity or mental health settings, are offered the service in any of the participating NHS Trusts within the five evaluation regions and have recorded notes available to the research team between December 2022 and March 2025 will be included in this analysis of individual patient data. While no formal sample size calculation was conducted, we estimate approximately 69 000 potential individuals for inclusion in the evaluation. This estimate was based on 11 participating NHS Trusts, approximately 7 months of data collection (taking into consideration potential data governance and submission delays/gaps), and a national smoking prevalence of 12.1% in England.

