#### Analysis

Findings will be reported descriptively. Frequencies and percentages (with 95% CI) will be reported. Subgroup analysis will be conducted and involve age, ethnicity, gender, regions, smoking status at admission, referral to in-house tobacco treatment team, tobacco care plan, onwards referral made, 28-day smoking status and smoking status at the time of delivery and at 36 weeks. We will also stratify findings by Lower Super Output Areas and Index of Multiple Deprivation, to explore whether there are inequalities in service delivery/uptake.

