## Discussion

We anticipate this mixed-method evaluation of a nationally provided tobacco dependence service to generate evidence regarding its implementation, drawn from all settings (i.e., acute hospital, maternity and inpatient mental health), across five regions in England. Localised and context-dependent implementation strategies, both successful and unsuccessful, will form recommendations for future iterations of this national policy. Moreover, the evaluation will support national-level assessment of the impact of the service on health outcomes, through planned statistical and health economic analyses. Taken together, integrated data from the various work packages will allow us to identify variations in service provision, and make recommendations for enhancing implementation, tailored to local contexts, to mitigate the risk of widening health inequalities. Our ongoing and sustained relationships with lay, clinical, policy, academic and practice partners will also support the co-production of key findings from this work, which will be disseminated widely, to advance research, policy and practice relating to addressing tobacco dependence in England.

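### WP 3 is asked for a change in quits, and WP 4 for a cost per additional quit, but the design has no comparator or baseline that could identify either

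*Protocol article*

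**What the plan says.** The objectives are in the protocol article, Evaluation aims and objectives, Table 2. WP 3 is "To estimate service effectiveness as the change in number of smokers who have undertaken an intervention" and have a 28-day quit, self-reported or confirmed by carbon monoxide (CO). WP 4 is "To estimate the cost-effectiveness of the service per additional quit". The WP 3 Design paragraph repeats the causal language: the study "aims to assess the reach of the service as well as the effect on health outcomes (effectiveness"). The Abstract also speaks of impact on outcomes for WP 3, and the Discussion says "the evaluation will support national-level assessment of the impact of the service on health outcomes".

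The design is fixed in the same article:

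- **Service start** (Evaluation aims and objectives): "Trusts participating in this evaluation started service implementation between February 2022 and November 2022".
- **Population** (WP 3, Population): smokers who "are offered the service in any of the participating NHS Trusts within the five evaluation regions" and who "have recorded notes available to the research team between December 2022 and March 2025".
- **Analysis** (WP 3, Analysis): "Findings will be reported descriptively". Counts and percentages with 95% confidence intervals follow, with subgroups and a breakdown by area deprivation.
- **Economics** (WP 4, Design and Analysis): costs are combined with WP 3 quit rates to give a cost per quit, if the data suffice. The word additional does not appear there.

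**The concern.** A change needs two states to compare, and an additional quit needs an estimate of how many people would have quit without the service. The article supplies neither for WP 3. Everyone analysed was offered the service. No pre-service records, comparison trusts or external benchmark are named, and no time contrast is planned. Pre-policy conditions are described only through WP 1 interviews and documents, which plan no baseline quit counts.

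The no-service quit rate is not negligible by default. The Introduction says smokers could already opt in to help, and that opt-out pathways had been recommended in maternity since 2010.

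What is at stake is the conclusion. A precise quit proportion reported against an effectiveness objective invites the reader to credit the service with every recorded quit. The same step in WP 4 would make a cost per recorded quit pass for a cost per additional quit. The limitations listed with the Abstract mention self-selected interviewees and restricted settings, but not the missing comparator.

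**Working it through.** **1. Timing.** Inputs: starts from February to November 2022 (Evaluation aims and objectives); records from December 2022 to March 2025 (WP 3, Population).

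- Length of window: 1 month in 2022 + 12 + 12 + 3 in 2025 = 28 months.
- From the latest start to the opening of the window: November to December 2022 = 1 month.
- From the earliest start to the opening of the window: February to December 2022 = 10 months.

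On these dates no participating trust contributes a month from before its start, and the earliest trust's first 10 months or so are not observed.

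**2. Population.** Restricting inclusion to smokers offered the service removes pre-service and unexposed patients whatever the dates mean.

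**3. The plan's own figure.** The article estimates about 69 000 people from 11 trusts, about 7 months and a prevalence of 12.1%, without a formal sample size calculation. Working backwards, 69 000 / 0.121 ≈ 570 248 admissions, and 570 248 / (11 × 7) ≈ 7 406 per trust per month. The article gives no admissions figure, so 69 000 can be neither reproduced nor refuted. The point does not depend on it.

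**4. What the missing comparator is worth.** The article gives no quit rate, so the rates here are assumptions for illustration. Let N = 69 000, observed quit proportion q = 20% and no-service proportion b.

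- Recorded quits: 0.20 × 69 000 = 13 800.
- Half-width of the 95% interval: 1.96 × √(0.20 × 0.80 / 69 000) ≈ 0.30 percentage points, or about 206 quits. This is a simple binomial interval that ignores clustering by trust. For q from 5% to 40% it runs from 0.16 to 0.37 points.
- Additional quits: (q − b) × N.
- Cost per additional quit relative to cost per recorded quit, for the same total cost: q / (q − b).

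| Assumed no-service rate b | Additional quits | Cost ratio |
|---|---|---|
| 0% | 13 800 | 1.00 |
| 5% | 10 350 | 1.33 |
| 10% | 6 900 | 2.00 |
| 15% | 3 450 | 4.00 |
| 20% | 0 | undefined |

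The planned data carry no information on b. The sampling interval spans a few hundred quits, and the range left open by b spans 13 800. A larger N narrows only the first.

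**The case against.** The strongest defence is that the article openly calls WP 3 non-randomised, observational and descriptive. Everyone enters as a smoker, so a recorded quit is a change in that person's status, and its count and percentage are what the analysis delivers. This stands as far as it goes: the quantity can be computed and is useful. It is not service effectiveness, because some of those smokers would have quit anyway.

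The second defence is that contrasts do exist. Offered is not the same as treated, the subgroups include referral and care plan, and a monthly trend could be tabulated. A reader might infer from this point that WP 3 can estimate nothing; that would be wrong. But the subgroup contrasts are crude, compare self-selected patients, and are not presented as the effectiveness analysis. No trend is planned, and one would show change under the service rather than because of it.

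The third is that the dates are softer than they look. The window refers to when notes are available to the researchers, and the start dates are a range across trusts, not dates per setting. That is fair, and it weakens the statement about months. It does not create a baseline, because the population is still limited to those offered the service.

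Two stronger readings are not supported:

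- A reader might infer that rising raw counts during roll-out will be taken as impact. The article plans percentages and no comparison of counts over time.
- A reader might take the smoking-at-delivery figures under Evaluation sites as a ready baseline. They are regional, dated 2022 (overlapping the start period), and measure prevalence rather than quitting among smokers. A before/after comparison on them would also be uncontrolled.

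The NHS England evaluation is called complementary, not a comparator.

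**Conclusion.** The point holds as a mismatch between objective and design. With the population, window and analysis that the article fixes, WP 3 can describe reach, uptake and quit proportions under the service. It cannot identify a change or additional quits attributable to the service, and WP 4 inherits this. No planned calculation is wrong; the fault lies in what the results are said to estimate.

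Under the assumed 20% quit rate, the unidentified part covers anything from none to all of 13 800 quits if the no-service rate lies between 0% and 20%. The conclusion that the change is not identified does not depend on those rates. It rests on the restriction to smokers offered the service and on the absence of any named baseline or comparator. It is not a detail that an analysis plan would ordinarily fill in, because the article itself settles the design.

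**What to change.** 1. Restate the WP 3 objective in Table 2, and the matching sentence in WP 3 Design, as: estimate the number and proportion of adult smokers offered the service (and of those referred and treated) with a recorded 28-day quit, self-reported and CO-validated, by setting and trust.
2. Restate the WP 4 objective as cost per recorded quit, in line with WP 4 Design and Analysis.
3. Remove or qualify effect, effectiveness and impact where they refer to WP 3 in the Abstract, WP 3 Design and Discussion, and add the lack of a comparator to the limitations.
4. Optionally, report monthly quit proportions by trust, labelled as a trend under the service, noting that up to about the first 10 months are unobserved for the earliest trust.

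Items 1 to 3 are wording only and need no new data. Item 4 is one further tabulation of the data planned for WP 3. The price is a more modest claim. If an effect is truly wanted, a pre-service or external comparator and an analysis to match must be added; the article gives no inputs from which to size that.

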### WP 4: health economic analysis (months 25–48)

#### Design

This quantitative non-randomised observational WP aims to explore the cost of offering the service and if sufficient high-quality data are available to estimate the return on investment in the form of a cost per quit.

The economic evaluation will be undertaken from the perspective of the healthcare provider. A costing analysis will be conducted to explore the cost of providing the service once it has been implemented in a trust.

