#### Analysis

The health economic analysis will take a bottom-up approach to estimate the cost of providing the service per service user once it has been implemented in the trust. Where sufficient data are available, a cost per quit will be estimated.

A model of a service user’s pathway through the service will be developed based on the draft pathways provided in the protocol. Each component of the pathway will be costed in collaboration with service managers. The pathway will be altered as required to meet the trust-specific service pathway. The cost for the full pathway will be calculated per service user.

The primary analysis will be at a trust level; however, if sufficient data are available, a pathway-specific cost for the three different pathways (acute, maternity, mental health) will be calculated.

The perspective of the costs will be the healthcare provider and will be based on the standard approach used in economic evaluation, which involves identifying, measuring and valuing all appropriate costs.^28^ Several cost categories will be considered, including staff costs (eg, tobacco treatment advisors) and ongoing non-staff costs (such as consumables and training courses). Costs will be calculated in Great British pounds corresponding to prices in the ‘cost year’ of the evaluation (2021/2022). Where required, relevant unit costs will be gathered from routine data sources.^29 30^

Where sufficient data are available, the costs of the intervention will be combined with the quit rates calculated in WP 3 to estimate a return on investment (in the form of an estimated cost per quit). Return on investment can be thought of as representing the ‘rate of return’ from an investment.^31^ If sufficient data are available regarding the different pathways (acute, maternity, mental health) a separate estimated cost per quit will be calculated for each pathway.

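### WP 4 promises cost-effectiveness per additional quit, but its design yields only a gross average cost per recorded quit, labelled a return on investment

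*Protocol article*

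**What the plan says.** The objectives in Table 2 (Evaluation aims and objectives) are worded as increments. For WP 4 the objective is "To estimate the cost-effectiveness of the service per additional quit". For WP 3, which supplies the quit data, it is "To estimate service effectiveness as the change in number of smokers who have undertaken an intervention" and have a self-reported or CO-confirmed 28-day quit.

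The WP 4 methods describe something different. The Design section says: "A costing analysis will be conducted to explore the cost of providing the service once it has been implemented in a trust". It then aims, if the data are good enough, to "estimate the return on investment in the form of a cost per quit". The Analysis section says: "Where sufficient data are available, a cost per quit will be estimated", and that "the costs of the intervention will be combined with the quit rates calculated in WP 3 to estimate a return on investment". Neither section uses the word *additional* or names a comparator, a background quit rate or a cost of earlier care.

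WP 3 fixes where the quit rates come from. Its Population section admits only smokers who were offered the service and gives a window of December 2022 to March 2025. Its Analysis section plans descriptive frequencies and percentages with 95% CIs.

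The Introduction describes care before the service: "the default model for tobacco dependence treatment was an opt-in approach where smokers could seek help to quit from healthcare professionals". Maternity is the stated exception, where opt-out pathways have been recommended since 2010.

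**The concern.** A cost per additional quit needs two differences: quits beyond those that would have occurred under earlier care, and costs beyond those of earlier care. The planned calculation has neither. It credits every recorded quit to the service and charges the service its full running cost.

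The label adds to the problem. The WP 4 Analysis section explains return on investment as a rate of return, but the planned output is a cost divided by a count of quits. No benefit or avoided cost is given a money value, so there is no return in it.

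The Discussion says the statistical and health economic analyses will support national-level assessment of the service's impact. A commissioner who reads a gross cost per quit against an objective worded per additional quit would take it for the incremental price of the service. Nothing in the output would correct that reading.

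**Working it through.** **Is there a figure in the plan to reproduce?** No. The article states no quit rate, background quit rate, unit cost or cost per quit. Its one planning figure, about 69 000 individuals, does not enter this point.

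**Can the design supply a counterfactual?**

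- Unexposed group: none. WP 3 and WP 4 both restrict the population to smokers offered the service.
- Pre-implementation period: none. Participating Trusts started between February and November 2022 (Evaluation aims and objectives), and the patient-data window opens in December 2022 (WP 3, Population). If that window is read as the period when notes were available, not when care was given, the restriction to people offered the service still excludes anyone treated before it existed.
- Comparative model: none. WP 3 is descriptive.
- External background rate or prior-care cost: none named in WP 4.

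**Notation.** C is the service cost per user and q the proportion of users with a recorded quit under the service. C0 is the cost per person of earlier care and b the quit proportion under earlier care.

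- Planned: C/q
- Promised: (C − C0)/(q − b)
- Promised ÷ planned: R = (1 − C0/C)/(1 − b/q)

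R = 1 only if C0 = 0 and b = 0, or if C0/C happens to equal b/q. R > 1 (the planned figure is too low) when C0/C < b/q. R < 1 (the planned figure is too high) when C0/C > b/q.

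**Numbers.** All values of q, b and C0/C below are assumptions.

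| q | b | R if C0 = 0, i.e. q/(q − b) | R at C0/C = 20% | R at C0/C = 40% | R at C0/C = 60% | Direction reverses above C0/C = b/q |
|---|---|---|---|---|---|---|
| 15% | 5% | 0.15/0.10 = 1.5 | 1.2 | 0.9 | 0.6 | 33.3% |
| 15% | 10% | 0.15/0.05 = 3.0 | 2.4 | 1.8 | 1.2 | 66.7% |
| 20% | 5% | 0.20/0.15 = 1.33 | 1.07 | 0.80 | 0.53 | 25% |
| 20% | 10% | 0.20/0.10 = 2.0 | 1.6 | 1.2 | 0.8 | 50% |
| 30% | 5% | 0.30/0.25 = 1.2 | 0.96 | 0.72 | 0.48 | 16.7% |
| 30% | 10% | 0.30/0.20 = 1.5 | 1.2 | 0.9 | 0.6 | 33.3% |

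Worked example at q = 20%, b = 5%: R = (1 − 0.20)/(1 − 0.25) = 1.07 when prior care cost 20% of the service, and (1 − 0.40)/(1 − 0.25) = 0.80 when it cost 40%.

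With no prior-care cost the planned figure is too low by a factor of 1.2 to 3.0. Once prior care has a cost, the same quit proportions can give an error in either direction.

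**The case against.** The best defence is that WP 4 is modest in its own text. It sets out to explore cost, makes every cost per quit conditional on sufficient data, and says each time what form its return on investment takes, so a reader can see which number will appear. WP 3 is openly descriptive and non-randomised. There is no decision threshold, and *additional* occurs in one cell of Table 2.

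That defence narrows the point but does not remove it. The data condition governs whether a cost per quit is produced; more records of the same kind supply no comparator. Nor is this detail that an article leaves to a fuller document, because the article itself fixes the population, window, analysis and calculation, and together they cannot meet its stated objective.

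The defence is right against several stronger readings that a reader might infer:

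- *The plan necessarily overstates value for money.* This holds only when C0/C < b/q. The article gives neither ratio, and the factor of 1.2 to 3.0 requires prior care to have cost nothing.
- *The error is greatest in pregnancy or acute illness because background quitting is high there.* The article gives no background quit rates, and the error depends on b/q and C0/C, not on b alone.
- *Maternity Trusts already ran an opt-out service.* The Introduction says such pathways were recommended, not that these Trusts delivered them.
- *Pathway comparisons will be distorted.* The primary analysis is at Trust level. Pathway figures are conditional, and WP 4 describes no ranking of pathways.
- *Leaving out set-up cost is an error.* Costing the service once implemented is a declared scope.

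**Conclusion.** The objective and the method contradict each other within the article. Table 2 promises an incremental result. The design can deliver only a gross average cost per recorded quit, and the term *return on investment* is a misnomer because no return is valued.

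This conclusion needs no assumed numbers. It rests on the stated population, the dates, the descriptive analysis, the planned combination of cost with quit rates, and the statement that support existed before the service.

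The size and direction of the gap cannot be computed from the article. They rest entirely on assumed q, b and C0. The average cost per recorded quit is a legitimate descriptive quantity; what fails is presenting it as the answer to the Table 2 objective.

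**What to change.** Reword the WP 4 objective in Table 2, and the matching statements in the WP 4 Design and Analysis sections, to *average cost per service user and per recorded quit*. Delete *additional* and *return on investment*.

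If an incremental figure is wanted, add a scenario analysis of (C − C0)/(q − b), clearly labelled as such. Vary both the background quit proportion and the prior-care cost over stated ranges, by pathway, since the Introduction describes different earlier care in maternity. Subtracting background quits alone would not give the promised quantity wherever C0 > 0. State the source of each range, and for maternity state what earlier care is assumed.

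The cost is some rewording, a small table if the scenario is kept, and a less ambitious stated objective. No new patient data are needed.
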